#### Analysis

2.9.2

We will assess plasma biomarkers related to AD, cardiometabolic biomarkers, cognitive function, energy and macronutrient intake, and diet quality at baseline, 6 and 12 months. We will assess cerebral antioxidants and brain volume at baseline and 12 months. We will calculate the mean, standard deviation, and 95% confidence intervals in both the intervention and control arms for each of these outcome variables at each time point, and for the change from baseline to each time point. This descriptive information will be summarized graphically which will aid in determining if, and when, differences in outcome variables arise among and across the two arms. Linear mixed models with an autoregressive correlation structure and a random intercept for each participant will be used to model the longitudinal serial correlation and baseline between‐subject variation. The model will include a main effect for intervention arm, and time and an arm‐by‐time interaction. The point estimate and 95% confidence interval for the arm‐by‐time interaction evaluated at both 6 and 12 months will be used to estimate the between arm effect size. Mixed models will be adjusted for age, sex, ethnicity/race, MVPA, premorbid ID, number of study participants living in the same household, intervention attendance, and intervention arm. Model fit will be assessed using diagnostic plots and comparing likelihood values between alternative model formulations or transformations, when appropriate. No multiplicity adjustment will be conducted since no hypotheses will be tested.

To determine the independent effects of weight loss or diet quality on changes in plasma biomarkers related to AD (Aβ 42/40, pTau217, and NfL), cerebral antioxidants, brain volume, cardiometabolic biomarkers, and cognitive function we will conduct a set of nested likelihood ratio tests (LRT). The goal of this analysis is to determine if weight loss, diet quality or both should be targeted in future trials for the prevention of AD in adults with DS. No adjustment for multiple testing will be conducted because rejection of any of the nested comparisons will imply that a change in a greater number of underlying covariates, for example, weight loss and diet compared to weight loss alone are needed to elicit changes in biomarkers.

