### Participant eligibility

2.2

To enhance generalizability, individuals with DS on medications for common chronic diseases (i.e., depression, hypertension, type 2 diabetes), using dietary supplements, or consuming a gluten‐free diet (i.e., celiac disease) will not be excluded. Random assignment should distribute these characteristics equally across interventions arms. Additionally, we will control for baseline characteristics in our analysis. Inclusion and exclusion criteria are provided in Table 2.

**TABLE 2 alz70219-tbl-0002:** Participant eligibility criteria for a 12‐month weight loss intervention in adults with Down syndrome.

Inclusion	
Residential status	Living at home with a parent/guardian or in a supported living environment with a family member, caregiver, or direct support professional who agrees to serve as a study partner for the entire 12‐month intervention
Age	18–64 years
Diagnosis	Down syndrome
BMI	25–50 kg/m^2^
Communication	Sufficient functional ability to understand directions, communicate preferences, wants, and needs through spoken language
Exclusion	
Dementia	Diagnosis of dementia as determined by the Dementia Screening Questionnaire for Individuals with Intellectual Disabilities (DSQIID)
Health concerns	Serious medical risk (e.g., recent cancer, recent heart attack, stroke, pregnancy, angioplasty) as determined by the health history form Insulin‐dependent diabetes Dairy allergy Swallowing disorders that require a thickened liquid diet
Medications	Individuals on GLP‐1 antagonist Individuals taking warfarin or other blood thinner medications Individuals taking anti‐amyloid medications or other medications related to the treatment of Alzheimer's disease
Other	Participation in a weight management program involving diet and PA in the past 6 months Unwilling to be randomized

Abbreviations: BMI, body mass index; GLP‐1, glucagon‐like peptide‐1; PA, physical activity.

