### Recruitment/Randomization

2.3

Project staff will contact local community agencies serving adults with DS, case managers, and Community Developmental Disabilities Organizations by mail/email, provide presentations at community agencies and local events, and distribute newsletters describing the project. Interested parents/guardians, caregivers, or adults with DS will be asked to contact the study coordinator via email, our website, or a dedicated toll‐free study phone number that will be included in all recruitment materials. The study coordinator will contact the interested individuals by phone to answer questions and conduct an initial eligibility screen. Video conference visits will be scheduled with those remaining interested, and potentially eligible, to obtain informed consent (participants or legal guardian) and participant assent (if not their own legal guardian) and determine final eligibility based on the DSQIID scores. Participants found to be ineligible will be provided with written materials describing available resources for weight loss. Participants will be stratified by age (18–30 vs. > 30 years) and sequentially computer‐randomized by the study statistician with 2:1 allocation to the weight loss or control arms. This randomization scheme was selected to include more participants in the weight loss arm which will allow for a larger sample size to assess the association of weight loss and changes in dietary intake with changes in biomarkers and cognitive function. Intervention assignments will be concealed and delivered to the study coordinator prior to participant orientation sessions described below.

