### Study partner role

2.4

Adults with DS receive assistance from family members and direct support professionals with decisions regarding meal planning, food shopping, and meal preparation, thus, playing an important role in the success of weight loss interventions in this population. For this trial, we will recruit either a parent/guardian, other family member, or direct support professional for those living in group homes to serve as a study partner for each participant. Study partners for participants in both intervention arms will be asked to attend the orientation and all monthly meetings with the interventionist and to provide transportation to our facilities for all outcome assessments. Study partners for participants in the weight loss arm will be asked to support, encourage, and assist participants in complying with the study protocol including the selection and preparation of foods consistent with the dietary recommendations, and assisting participants with self‐monitoring of both dietary intake and body weight.

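### The household-count covariate handles neither diet spillover between housemates nor the dependence between their changes; the arm effect may be diluted and the Aim 3 tests run slightly liberal

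*Protocol article*

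**What the plan says.** All references are to the protocol article.

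- **Allocation (2.3 Recruitment/Randomization).** Participants are "sequentially computer‐randomized by the study statistician with 2:1 allocation to the weight loss or control arms". The only stratum is age: "Participants will be stratified by age (18–30 vs. > 30 years". No rule for housemates is stated.
- **Where participants live (Table 2; 2.4 Study partner role).** Eligible settings are "Living at home with a parent/guardian or in a supported living environment with a family member, caregiver, or direct support professional". Section 2.4 foresees a "direct support professional for those living in group homes to serve as a study partner for each participant".
- **How the diet is delivered (2.4).** In the weight-loss arm the study partner helps the participant comply, "including the selection and preparation of foods consistent with the dietary recommendations". Control sessions (2.5.2) give information and request no lifestyle change.
- **Analysis (2.9.2).** The models are "Linear mixed models with an autoregressive correlation structure and a random intercept for each participant". The effect is read from the arm-by-time interaction at 6 and 12 months. Household enters only through the adjustment list, as the "number of study participants living in the same household". Aim 3 uses nested likelihood ratio tests on weight loss and diet quality. No household random effect or clustered variance is named.
- **Sample size (2.9.1).** The simulation also uses only a participant random intercept.

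**The concern.** A covariate that counts co-resident participants has a purpose only if some households may contribute more than one. Two problems then arise, and the count solves neither.

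**Spillover.** A control who shares a kitchen with a weight-loss participant may eat part of the intervention diet. This shrinks the contrast that the trial exists to estimate, and the estimate is meant to inform a larger trial. The count takes the same value for a control whose housemate is also a control and for one whose housemate is in the weight-loss arm, so it cannot identify the exposed controls. As worded, it is also a main effect: it shifts all visits equally and does not act on the arm-by-time term.

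**Dependence.** Housemates share food, carers and routine, so their changes may be correlated. A fixed covariate moves the mean and leaves that residual correlation in place. Whether this harms inference depends on the quantity being estimated, and the working takes the arm contrast and Aim 3 separately.

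**Working it through.** **1. The plan's own figures.** Assumed annual NfL change is 3% in controls and 1.35% in the intervention arm, a difference of 1.65 points. Cohen's h = 2·asin(√0.03) − 2·asin(√0.0135) = 0.115, which agrees with the stated 0.12. The 95% CI width of 3 points cannot be reproduced independently because no SD is given. It implies SE = 1.5/1.96 = 0.765. With 20% attrition (43.2 and 21.6 completers), the implied SD of annual change is 0.765/√(1/43.2 + 1/21.6) = 2.90 points.

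**2. Chance that a control is exposed.** Under independent 2:1 allocation, P(at least one weight-loss housemate) = 1 − (1/3)^k for k co-enrolled housemates: 67%, 89% and 96% for k = 1, 2, 3. A two-participant household is split between arms with probability 2·(2/3)·(1/3) = 44%.

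**3. Dilution.** Dilution = (share of controls with one co-enrolled housemate) × 2/3 × (spillover fraction). Share and spillover are assumed.
- Low: 0.10 × 2/3 × 0.25 = 1.7%, so 1.65 becomes 1.62.
- High: 0.30 × 2/3 × 0.50 = 10%, so 1.65 becomes 1.485.

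**4. Does the count remove it?** A simulation of 65 completers (43:22, SD 2.90, 4,000 runs per cell) regressed change on arm and household count. This treats the covariate generously, because the count was allowed to act on change directly.

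| Participants sharing | Spillover | Mean estimate (true 1.65) | Coverage of 1.65 |
|---|---|---|---|
| 40%, in pairs | 50% | about 1.43 | about 94% |
| 40%, in pairs | 100% | about 1.19 | about 91% |
| 40%, in fours | 50% | about 1.35 | about 93% |
| 40%, in fours | 100% | about 1.06 | about 88% |

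For pairs at 50%, direct arithmetic gives 1.65 × (1 − 0.40 × 2/3 × 0.50) = 1.43. The bias is what it would be with no covariate. These scenarios are more severe than those in step 3 and show the mechanism, not the expected size.

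**5. Correlation and the arm contrast, individual allocation.** In the difference in means, a weight-loss participant has weight 3/(2N) and a control −3/N. For two housemates the expected product of weights is (4/9)·9/(4N²) + (1/9)·9/N² − (4/9)·9/(2N²) = (1 + 1 − 2)/N² = 0. Positive correlation therefore cancels on average. The simulation agrees: with no spillover and ICC 0.3–0.5, empirical SE is 0.76–0.77 against model SE 0.75–0.76, with coverage 94–95%.

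**6. Correlation and the arm contrast, housemates allocated together.** At ICC 0.5 with 40% sharing and the count covariate only, empirical SE is 0.87 against model SE 0.78 for pairs (coverage 92%), and 0.98 against 0.79 for fours (coverage 89%).

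**7. Aim 3.** Weight change and diet quality are not randomised and may themselves cluster by household. The variance inflation for a slope is about 1 + share × (m − 1) × ICC(exposure) × ICC(outcome), where m is household size. The true size of a nominal 5% test is then 2·[1 − Φ(1.96/√inflation)]. With 40% sharing (ICCs assumed):
- pairs, both ICCs 0.3: inflation 1.036, size 5.4%
- pairs, both ICCs 0.5: inflation 1.10, size 6.2%
- fours, both ICCs 0.3: inflation 1.108, size 6.3%
- fours, both ICCs 0.5: inflation 1.30, size 8.6%

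Simulation of such tests gave about 5–8%.

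**The case against.** **A reader might infer that ignored clustering makes the main confidence intervals too narrow.** For a same-arm pair with ICC 0.1–0.3, the ratio of naive to correct width is 1/√(1 + ICC), or 0.95 to 0.88, which looks like 5–12%. This leaves out the 44% of pairs that would be split, where the naive interval is too wide. Step 5 shows that the two cancel for the arm contrast, so that reading fails under the allocation the article describes.

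**A reader might also infer that households should have been randomised.** The article does not support this as a requirement. If the first enrollee's assignment passed to later housemates, they and their partners could know the arm before consenting, which weakens the concealment described in 2.3 and claimed as a strength in the Discussion. It also costs precision (step 6). On mean squared error the choice is close. At 10% dilution, individual allocation gives 0.765² + 0.165² = 0.585 + 0.027 = 0.61. Household allocation with 30% in pairs gives 0.585 × (1 + 0.30 × 0.3) = 0.64 at ICC 0.3 and 0.585 × (1 + 0.30 × 0.1) = 0.60 at ICC 0.1.

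**Other objections that stand in part.**
- The article gives no household counts, ICC or spillover size, and the covariate shows only that co-enrolment is allowed for. A support worker shared across arms is possible but not stated.
- Individual allocation of housemates is read from participant-level wording. A housemate rule could sit in the full protocol, which is not shown.
- Counselling, calorie goals, app and shakes are individual, which limits spillover. Diet and skin carotenoids are measured in both arms at every visit, so spillover could be looked for, provided exposed controls are identified.
- The article nowhere claims that the count deals with contamination or correlation.
- A dilution of 0.03–0.17 points is small beside a CI half-width of 1.5 points.

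None of this rescues the count. The analysis section does specify how households are handled, and that specification does neither job.

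**Conclusion.** The point holds in a limited form. The household count neither identifies exposed controls nor models dependence between housemates' changes.

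- **Spillover** is the main issue: bias toward zero of about 2–10% of the arm effect under the assumed ranges (10–30% of controls with one co-enrolled housemate, 25–50% spillover). It would be larger with more sharing and nil if no controls have co-enrolled housemates.
- **Between-arm interval:** practically unaffected by unmodelled correlation if housemates are allocated individually. It would be too narrow if they are allocated together (coverage 89–92% at ICC 0.5 with 40% sharing).
- **Aim 3 tests:** modestly anti-conservative, at about 5–8% for a nominal 5%, if exposure and outcome both cluster by household.

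Every size here rests on assumed household shares, ICCs and spillover. The change is worth making because it is cheap and the trial's product is an effect estimate for planning.

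**What to change.** 1. **Models.** In 2.9.2, replace the household-count covariate with household-level dependence that acts on change, in all models including Aim 3. Use either a household-by-time random effect or household-clustered standard errors with a small-sample correction. A household random intercept alone is not enough, because it cancels out of within-person change. Clustered standard errors do not carry into a likelihood ratio test, so if that route is taken Aim 3 needs a cluster-robust Wald test instead.
2. **Data.** Record a household identifier and, for each control, whether a weight-loss participant lives in the same household.
3. **Sensitivity analysis.** Prespecify a repeat of the main analysis excluding mixed-arm households.
4. **Allocation.** State the rule for housemates. Allocating them together is an option only if all co-residents consent before the household's assignment is revealed. It carries the precision cost in step 6 and makes item 1 essential. It is not a required change.

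Cost: one data field, model wording, slightly wider intervals in some models, and a smaller sample in the sensitivity analysis. Items 1 to 3 need no change to the randomisation; if enrolment is complete, the household data can be collected retrospectively.

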### Overview of study design

2.1

This is a 12‐month randomized trial in 81 non‐demented adults with DS. Participants will be randomized (2:1) to either a weight loss or a general health education control group. The weight loss arm will follow the protocol used in our previous trials,^16^, ^17^, ^18^ plus recommendations from the MIND diet,^13^, ^14^ to increase antioxidant consumption and further improve diet quality. Participants and a study partner will be asked to attend monthly behavioral counseling/education sessions with a trained interventionist delivered remotely using Zoom video conferencing (San Jose, CA, USA) and self‐monitor diet and body weight using commercially available Web‐based applications. Participants and a study partner in the control arm will be asked to attend monthly behavioral counseling/education sessions with a trained interventionist delivered remotely and will receive education on general health education topics such as injury prevention, oral health, sleep, hydration, exercise and physical activity, and healthy eating. Outcomes assessed across 12 months will include (1) biomarkers related to AD including plasma amyloid beta 42:40 ratio (Aβ 42/40), phosphorylated Tau (pTau217), neurofilament light (NfL), and glial fibrillary acidic protein (GFAP); (2) cognitive function using both directly‐administered and informant‐based assessments; (3) cardiometabolic biomarkers such as lipid levels, blood glucose levels, and inflammatory markers; (4) cerebral antioxidants and brain volume assessed by magnetic resonance spectroscopy; and (5) dietary intake assessed using 3‐day photo‐assisted food record and skin carotenoid content using a Veggie Meter. Our analysis will include three aims (Table 1). This trial will provide preliminary data on the impact of weight loss and improved diet quality on cognitive function and factors associated with the development of AD.

**TABLE 1 alz70219-tbl-0001:** Study aims for a 12‐month weight loss intervention in adults with Down syndrome.

Aim 1	Calculate effect sizes for changes in plasma biomarkers related to AD, cardiometabolic biomarkers, and cognitive function in both intervention arms across 12 months.
Aim 2	Calculate effect sizes for changes in cerebral antioxidants and brain volume in a subsample of participants in both intervention arms across 12 months.

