#### Sample size

2.9.1

The primary aim is to estimate the effect of a 12‐month weight loss intervention relative to control to determine if the intervention impacts relevant outcome variables, and if so, to precisely quantify the observed effect. The sample size was estimated using simulation with regard to plasma NfL based on the observation that changes in this biomarker is an early marker of AD in adults with DS.^2^ A recent 2021 paper reported an annual change in NfL of 3% in asymptomatic non‐progressive AD patients.^43^ Thus, we simulated annual data at baseline, 6 and 12 months assuming an average 3% annual increase in NfL for all participants in the control arm and an average change of 1.35% in the intervention arm which corresponds to a “small” Cohen's h effect size of 0.12. We modeled the between arm difference in NfL using a linear mixed model with a random intercept for each participant; with a sample size of 81 (*n* = 54 intervention; *n* = 27 control) and an estimated attrition rate of 20%. With these assumptions, we will be able to estimate the precision of the difference in the annualized increase in NfL with a 95% confidence interval of width 3%. Similar mixed models will be fit for all seven outcome variable categories to estimate the effects across all the domains of interest. A major concern with using estimated effects from pilot studies to power larger trials is that they are highly variable. This sample size and approach will guarantee good precision for our estimates which is especially important considering that there are currently no data regarding clinically relevant changes to use for powering a larger trial.

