Completion of this project represents an initial step toward developing and disseminating effective interventions to prevent or delay the development of AD in adults with DS. This trial will provide preliminary data on the impact of weight loss and improved diet quality on cognitive function and factors associated with the development of AD and the time course of any changes in adults with DS. Additionally, results of this study could help inform dietary guidelines for adults with DS. If the results of this pilot are positive, that is, improvements in some or all AD associated outcomes assessed we will propose an adequately powered randomized trial to further investigate the impact of weight loss and diet quality on these outcomes in adults with DS. If our pilot results suggest an independent effect of diet quality on factors associated with AD we will also propose an adequately powered randomized trial to investigate the impact of improved diet quality without weight loss on AD outcomes. Subsequent trials may include additional AD markers obtained from cerebrospinal fluid (CSF) or PET scans.

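### Aim 3 reads nested tests on post-randomisation weight and diet-quality change as causal and uses them to pick future targets, but the design supports only associations

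*Protocol article*

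**What the plan says.** Section 2.1 randomises one thing: "Participants will be randomized (2:1) to either a weight loss or a general health education control group". The weight loss arm follows the group's earlier energy-reduced diet protocol "plus recommendations from the MIND diet", so both dietary elements sit in the same arm.

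Section 2.9.2 introduces a set of nested likelihood ratio tests "To determine the independent effects of weight loss or diet quality on changes in plasma biomarkers related to AD", and on imaging, cardiometabolic and cognitive outcomes. The stated goal is "to determine if weight loss, diet quality or both should be targeted in future trials for the prevention of AD in adults with DS". The same paragraph justifies the absence of a multiplicity adjustment by saying that rejecting a nested comparison implies that change in more of the factors (for example weight and diet, not weight alone) is necessary to produce biomarker change.

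The Discussion attaches a decision to the result: "If our pilot results suggest an independent effect of diet quality on factors associated with AD we will also propose" a randomised trial of better diet quality without weight loss.

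Two places use softer language. Table 1 says Aim 3 will explore these effects. Section 2.3, explaining the 2:1 ratio, says the larger arm serves "to assess the association of weight loss and changes in dietary intake with changes in biomarkers and cognitive function".

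**The concern.** Randomisation protects the comparison of arms. It does not protect a comparison of participants who lost more weight with those who lost less, or of those whose diet improved more with those whose diet improved less. Those differences arise after randomisation, and anything that influences both the change and the outcome can produce them. No randomised contrast separates weight from diet quality, because one arm receives both.

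A likelihood ratio test that is correctly computed on such data tests conditional association. It cannot tell an effect of diet quality from a shared cause, or from outcome change driving diet and weight change. Section 2.9.2 nevertheless fixes a causal reading of a rejection and a use for it. At stake is which factor goes into the next trial.

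**Working it through.** **Is there a plan figure to reproduce?** None exists for Aim 3. Section 2.9.1 gives figures for the arm contrast only. The quoted effect size reproduces: 2·asin(√0.03) − 2·asin(√0.0135) = 0.115, which rounds to 0.12. The 95% interval width of 3% cannot be reproduced because no standard deviation is given. Neither figure bears on this point.

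**Inputs from the document.** 54 + 27 participants and 20% attrition give 54 × 0.8 = 43.2 and 27 × 0.8 = 21.6, so about 43 + 22 = 65 completers.

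**Assumptions, not in the document.** A 5% test level; a between-arm shift of 0.8 SD in both weight change and diet-quality change; arm kept in the model; and a single unmeasured cause with the same loading *l* on weight change, diet change and outcome change. The true effect of weight and of diet on the outcome is zero.

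**The relevant test.** An independent effect of diet quality corresponds to diet added to a model that already contains weight. Within arm, every pair of the three variables has correlation *l*². The partial correlation of diet with outcome given weight is therefore

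(*l*² − *l*⁴)/(1 − *l*⁴) = *l*²/(1 + *l*²).

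The test rejects when 65·ln(RSS₀/RSS₁) > 3.84, that is when the sample partial correlation exceeds √(1 − e^(−3.84/65)) = 0.240 in absolute value. On the Fisher scale, with √(65 − 3 − 2) = √60 = 7.746, the threshold is atanh(0.240) × 7.746 ≈ 1.89.

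| Loading *l* | Partial correlation | Fisher z × √60 | Rejection, approximation | Rejection, simulation (4,000 runs) |
|---|---|---|---|---|
| 0 | 0 | 0 | 5.8% | 5.0% |
| 0.3 | 0.083 | 0.64 | 11.1% | 10.8% |
| 0.4 | 0.138 | 1.08 | 20.8% | 20.4% |
| 0.5 | 0.200 | 1.57 | 37.4% | 38.0% |

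A second, separately written simulation gave 12%, 21% and 38% for the three non-zero loadings. Weight added to diet behaves almost identically (38.6% at 0.5).

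**Reverse ordering.** Suppose instead that outcome change drives both weight change and diet change, with correlation *r*. The partial correlation is then *r*/√(1 + *r*²), and diet added to weight rejects 35.4%, 65.8% and 87.6% of the time at *r* = 0.2, 0.3 and 0.4 (assumed values).

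**Does the handling of arm cure it?** No.
- Leaving arm out lowers the shared-cause figure at 0.5 from 38.0% to 28.4%.
- It also lets any other action of the package be credited to weight or diet. With no shared cause, a 0.5 SD package effect by another route, and assumed arm shifts of 1.0 SD in weight and 0.6 SD in diet, weight added to diet rejects 12.2% without arm and 5.4% with arm.
- With arm in the model, only within-arm, non-randomised variation remains.

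**Does time ordering cure it?** Only in part. Using the 0–6 month weight change to predict the 12-month outcome given the 6-month outcome, with a shared cause that persists over both halves of the year, the test of weight still rejects about 11%, 20% and 38–39% at loadings 0.3, 0.4 and 0.5.

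**The case against.** **Exploratory status.** Table 1 says explore, section 2.3 says association, and the Discussion calls the study an exploratory pilot. The main follow-on trial rests on improvement in outcomes; the diet-quality trial would be an additional proposal, itself randomised and adequately powered. This stands, and it limits the consequence. A reader might infer that Aim 3 by itself launches a trial or yields a confirmatory claim; the Discussion does not go that far. The softer wording does not cancel the rule in section 2.9.2, which says what a rejection implies and what it is for.

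**The model is not fully described.** Timing and covariates of the nested tests may be set in an analysis plan that is not shown, and same-visit analysis is only inferred from Table 3. This stands too, so missing model detail is not the criticism. No choice of lag or covariates would make a rejection carry the stated causal meaning.

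**Adjustment is planned.** The arm-effect models adjust for age, sex, ethnicity/race, physical activity, premorbid intellectual disability, participants per household, attendance and arm. If carried over, these would remove some confounding, and attendance may partly capture engagement. They would remove only what is measured, and they do not address reverse ordering.

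**Specific bias routes.** Section 2.4 says "Study partners for participants in the weight loss arm will be asked to support, encourage, and assist participants in complying with the study protocol", and study partners also supply the informant ratings. A reader might infer that partner engagement biases every outcome. Through the ratings it can reach only the informant-rated scales, not plasma, imaging or the directly administered tests. A reader might also infer from the self-monitoring text that adherence depends on the participant's ability. That text does not say so: logging is optional and partner-assisted, and dementia is an exclusion.

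**Conclusion.** The concern holds as a point about what Aim 3 can conclude. Section 2.9.2 gives a causal meaning, and a role in choosing targets, to tests that estimate associations between post-randomisation changes and outcomes.

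The size depends on assumptions. With no true effect, diet added to weight rejects about 11–12%, 20–21% and 38% of the time at assumed shared-cause loadings of 0.3, 0.4 and 0.5, against a nominal 5%. The documents give no basis for choosing among these loadings, and the arm shifts are assumed as well.

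Larger figures are tempting but do not describe this claim. Weight tested alone rejects 12%, 27% and 54% at the same loadings, but that is not a test of an independent effect. The chance that at least one of three comparisons rejects is already 11% with no shared cause, which is multiplicity and a separate matter.

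The harm is a misdirected choice of target for a later randomised trial.

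**What to change.** 1. In Table 1, section 2.9.2 and the Discussion, replace the wording about independent effects, and about changes being needed to bring about biomarker change, with *associations*, in line with section 2.3.
2. State in section 2.9.2 and the Discussion that these tests alone do not select the target of a future trial.
3. Keep arm, the baseline value of the outcome, and the baseline covariates already listed in section 2.9.2 (age, sex, ethnicity/race, premorbid intellectual disability, participants per household) in every Aim 3 model.
4. Optionally, for outcomes measured at three visits, report a lagged model (0–6 month change in weight and diet quality predicting the 12-month outcome given the 6-month outcome) as a sensitivity check on reverse ordering only. Imaging has two visits, so this is not available there. Do not treat agreement in direction between lagged and concurrent estimates as grounds for naming a target. In a simulation with no true effect and a persistent shared cause at loadings 0.3, 0.4 and 0.5, such agreement was present in 96%, 97% and 98% of the false concurrent rejections.

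The cost is wording plus, if wanted, one extra model per outcome on data already scheduled. The downside is a weaker stated conclusion for Aim 3.
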